## Abstract

**Background:**

Older patients (≥65 years old) experience high rates of adverse outcomes after an emergency department (ED) visit. Reliable tools to predict adverse outcomes in this population are lacking. This manuscript comprises a study protocol for the Risk Stratification in the Emergency Department in Acutely Ill Older Patients (RISE UP) study that aims to identify predictors of adverse outcome (including triage- and risk stratification scores) and intends to design a feasible prediction model for older patients that can be used in the ED.

**Methods:**

The RISE UP study is a prospective observational multicentre cohort study in older (≥65 years of age) ED patients treated by internists or gastroenterologists in Zuyderland Medical Centre and Maastricht University Medical Centre+ in the Netherlands.

After obtaining informed consent, patients characteristics, vital signs, functional status and routine laboratory tests will be retrieved. In addition, disease perception questionnaires will be filled out by patients or their caregivers and clinical impression questionnaires by nurses and physicians. Moreover, both arterial and venous blood samples will be taken in order to determine additional biomarkers. The discriminatory value of triage- and risk stratification scores, clinical impression scores and laboratory tests will be evaluated.

Univariable logistic regression will be used to identify predictors of adverse outcomes. With these data we intend to develop a clinical prediction model for 30-day mortality using multivariable logistic regression. This model will be validated in an external cohort.

Our primary endpoint is 30-day all-cause mortality. The secondary (composite) endpoint consist of 30-day mortality, length of hospital stay, admission to intensive- or medium care units, readmission and loss of independent living.

Patients will be followed up for at least 30 days and, if possible, for one year.

**Discussion:**

In this study, we will retrieve a broad range of data concerning adverse outcomes in older patients visiting the ED with medical problems. We intend to develop a clinical tool for identification of older patients at risk of adverse outcomes that is feasible for use in the ED, in order to improve clinical decision making and medical care.

**Trial registration:**

Retrospectively registered on clinicaltrials.gov (NCT02946398; 9/20/2016).

**Electronic supplementary material:**

The online version of this article (10.1186/s12877-019-1078-2) contains supplementary material, which is available to authorized users.

## Background

Older patients (≥65 years of age) constitute an increasing population in emergency departments (EDs). They experience more adverse outcomes than younger ED patients [1–3] as their ED visits are often highly urgent and followed by hospitalization, Intensive Care Unit (ICU) admission, readmission, and mortality (up to 10% within 3 months). In older ED patients with internal medicine (medical) problems, mortality is even higher (23.8% in 3 months) [4].

Risk stratification can be used to identify ED patients who are at high risk of adverse outcomes. This may lead to improvement in medical care and outcome by early start of interventions [5]. Several risk stratification scores have been developed for the older ED population, such as the Identification of Seniors at Risk (ISAR) [6] or Triage Risk Stratification Tool (TRST) [7]. Unfortunately, these scores do not accurately identify those who experience adverse outcomes (areas under the curve (AUCs) range from 0.59–0.74) [8–10]. Triage systems (e.g. Manchester Triage System (MTS) [11]) are also used in the ED population but they tend to undertriage older patients [12]. Furthermore, risk stratification scores either applicable to the general ED population (e.g. Acute Physiology and Chronic Health Evaluation II (APACHE II) score [13]) or to patients with specific diseases (e.g. Abbreviated Mortality ED Sepsis (abbMEDS) score [14] for sepsis) are used. However, these are not validated in the older ED population.

It may be possible that older patients at risk of adverse outcomes can be identified by assessing the disease perception of patients (or caregivers) or clinical intuition or impression of physicians and/or nurses. Indeed, both disease perception and clinical impression are shown to be associated with mortality and morbidity [15–20]. Unfortunately, most studies were conducted in other clinical settings than the ED (e.g. admission units and ICUs) [4, 17, 20] and in younger patients [17, 18, 20]. A second method to assess clinical impression is to ask the ‘surprise question’ (SQ): ‘Would I be surprised if this patient died within the next 12 months?’. The SQ has been studied in cancer and renal failure patients but its diagnostic accuracy for one-year mortality varies considerably [21]. The predictive value of the SQ for short-term mortality in older medical ED patients is unknown.

Laboratory tests may also be useful for identification of older patients at risk of adverse outcomes [4, 22]. In addition, non-routine laboratory tests, such as lactate, high-sensitivity cardiac troponin T (hs-cTnT), N-terminal pro-B-type natriuretic peptide (NT-pro-BNP), procalcitonin (PCT) and d-dimer, may be valuable predictors of adverse outcome as well [23–27]. Since these tests are indicators of serious conditions and diseases (e.g. tissue hypoperfusion, myocardial injury, bacterial infection and thromboembolism) and often present in the older ED population, we hypothesize that these tests can be useful as predictors. Until now, most studies regarding the predictive value of these tests were performed retrospectively [24, 28–33] or in selected, mostly younger, patients [30–38].

We hypothesize that in the early stage of an ED visit, when important treatment decisions have to be made, several factors can predict adverse outcomes. The aims of this multicentre, prospective study are to 1) identify early predictors of adverse outcome in older ED patients, and 2) develop a clinical prediction model for 30-day mortality.

## Methods/design

### Study design and setting

This prospective multicentre observational cohort study will take place at the EDs of Zuyderland Medical Centre (MC) Heerlen and Maastricht University Medical Centre+ (MUMC+), in the Netherlands. Zuyderland MC is a secondary teaching hospital with 635 beds and 30,000 ED visits/year. MUMC+ is a secondary and tertiary teaching hospital with 700 beds and approximately 23,000 ED visits/year.

### Study population

All patients ≥65 years of age, assessed and treated by an internist or gastroenterologist at the EDs during the study period, are eligible for study inclusion. We chose medical ED patients because these patients are at high risk of adverse outcomes after an ED visit [4]. We intend to include 450 patients in Zuyderland MC starting from July 2016, and 150 patients in MUMC+ from September 2016.

Inclusion criteria:Age ≥ 65 yearsTreatment by an internist, gastroenterologist (or emergency physician under supervision of an internist/gastroenterologist)Informed consent

Exclusion criteria:Earlier participation in this studyNo informed consentInability to speak Dutch or EnglishAdmission to a ward of another specialty than internal medicine/gastroenterology

In case a patient is unable to provide informed consent, e.g. in case of delirium, dementia or when a patient is too severely ill to answer the questions, a legal representative can provide informed consent. A legal representative can either be a legal guardian or an immediate family member including their spouse, adult children, parents or adult siblings. The determination, whether or not a patient can provide informed consent for them self, will be based on expect opinion by the attending physician or investigator. Objection by an incapacitated patient or his/her representatives will always lead to exclusion from the study and analysis.

### Objectives and outcome

#### Objectives

Evaluation of the discriminatory value for adverse outcomes of:triage and risk stratification scores:Triage score: MTS [11]General risk stratification scores: APACHE II [13], ISAR score [6] and ISAR-Hospitalised Patients (ISAR-HP) score [39]Disease specific scores: Glasgow-Blatchford Bleeding Score (GBS) [40], abbMEDS score [14], Sepsis-related Organ Failure Assessment (SOFA) score [41] and Confusion, Urea, Respiration, Blood pressure, Age > 65 years (CURB-65) score [42]clinical impressions of nurses and physicians, SQ and disease perception of patientsroutine and non-routine laboratory resultsDevelopment and validation of a prediction model for short-term mortality and test the predictive ability of this model for the other adverse outcomes/endpoints

#### Outcomes

Primary endpoint:30-day (both in- and out-hospital) all-cause mortality

Secondary endpoints:Secondary composite endpoint:30-day mortalityLength of hospital stay (LOS) > 7 daysIntensive or medium care unit (ICU/MCU) admissionUnplanned readmission within 30 days after dischargeLoss of independent living (e.g. discharge to a nursing home/hospice or with palliative care in previously community dwelling patients)1-year all-cause mortality

### Study procedures

#### Inclusion of patients

After arrival at the ED, all eligible patients will receive an information brochure and will be asked to participate in the study by the attending physician or investigator. Informed consent must be signed by the patient or his/her legal representative before entering the study. Figure 1 details the study procedure.

**Fig. 1 Fig1:**
[figure not shown]
Flow chart of study procedure

#### Questionnaires

The patient/caregiver will receive a questionnaire at the ED that should be filled out as soon as possible. This questionnaire (Additional file 1) contains four questions regarding disease and health perception. The nurse and attending physician both receive a similar questionnaire (Additional files 2 and 3) that has to be filled out before history taking and physical examination and without knowing any diagnostic results. This questionnaire contains six questions regarding the first clinical impression including the SQ. When a patient is admitted to the hospital, a fourth questionnaire (Additional file 4), containing ten questions about the patients’ daily functioning, will be filled out the next day. This questionnaire is used to calculate the ISAR-HP and Katz Activities of Daily Living (ADL) [43] index score. The results of the questionnaires will only be available for the investigators.

#### Blood sample collection

In addition to routine blood sampling, two venous blood samples and an arterial blood gas sample will be collected at the ED. Venous blood samples will be stored in a freezer at − 20 degrees Celsius and will be analysed for hs-cTnT, NT-pro-BNP, PCT and d-dimer after 4–12 weeks. Results will be blinded for the physician. Results of the arterial blood gas and lactate level analysis will be presented to the attending physician. Additional venous and arterial blood sample collections will only be performed in Zuyderland MC.

#### Data collection and follow up

Study parameters will be retrieved from the patient’s medical electronic record and questionnaires. All patients will be followed up for 1 year to obtain long-term outcomes. The following parameters will be collected:

*Study parameters collected at the ED:*
Demographics (age, sex)Date and time of ED visit and transport to the EDComorbidities: Charlson Comorbidity Index [44], smoking status and presence of cardiovascular disease in family historyVital signs: heart rate, blood pressure, respiratory rate, oxygen saturation, temperature, Glasgow Coma Scale [45]First clinical impression (including the SQ) of the physician/nurse and disease perception of the patient/caregiver using questionnairesCognitive functioning (dementia, mild cognitive impairment, delirium or normal) based on the diagnosis of a geriatrician and/or on medical recordsNumber of visits to the hospital in the preceding yearMedication use before the ED visitTime spent at the ED and the number of physician consultations and radiological examinations during ED stayRoutine laboratory tests: glucose, creatinine, blood urea nitrogen, sodium, potassium, chloride, bicarbonate, calcium, phosphate, bilirubin, alkaline phosphatase, gamma- glutamyltransferase, aspartate transaminase, alanine transaminase, lactate dehydrogenase, albumin, c-reactive protein, hemoglobin, hematocrit, leukocyte count, platelet count, international normalized ratio and activated partial thromboplastin timeNon-routine laboratory tests: arterial blood gas, lactate, hs-cTnT, NT-pro-BNP, PCT and d-dimerTriage score: MTSGeneral risk stratification scores:APACHE II scoreISAR scoreDisease specific stratification scores:GBS for upper gastrointestinal bleedingabbMEDS score for sepsisSOFA score for sepsisCURB-65 score for pneumonia

These scores were only calculated when the specific disease for which the score was developed was present.Diagnosis at the time of discharge from the ED

*Study parameters collected in admitted patients only:*
Functional capability:Katz ADL index scoreISAR-HP scoreDiagnosis at time of discharge from the hospitalLOS (days)Living arrangement after discharge: e.g. community dwelling, nursing- or care home etc.

Follow up study parameters collected in all participants:ICU/MCU admissionAll-cause mortality within 30 days of the ED visitReadmission within 30 days after dischargeAny new relevant medical condition within 1 year after ED visit (e.g. new diagnose of venous thromboembolism, cardiovascular disease or malignancy)

#### Possible selection bias

Because physicians must give priority to providing emergency care when the ED is crowded, we expect that not all possible candidates can be included. To investigate possible selection bias, we will retrospectively form a sample of non-included patients and collect the same data, except for the non-routine tests and questionnaires, as in our prospective cohort population. For practical reasons, we intend to include the first 200 non-included candidates in this retrospective sample. Patients who refused to participate in the study will not be included. Baseline characteristics (age and sex) will be analysed for all (non-included) candidates to investigate possible selection bias as well.

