### Trial status

As of 22/12/2018, the study is still ongoing; we are about to finish the inclusion of patients for the validation cohort and are completing 1 year follow up. A total of 603 participants are included in the derivation cohort from July 2016 until the beginning of February 2017 in the two participating centres. In Zuyderland MC, 450 patients, and in MUMC+, 153 patients are included.

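### The selection-bias sample is the earliest 200 missed candidates, so beyond age and sex it may not represent later recruitment months or MUMC+

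*Protocol article*

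**What the plan says.** Under Possible selection bias, the protocol article gives the reason for the check: "Because physicians must give priority to providing emergency care when the ED is crowded, we expect that not all possible candidates can be included". The remedy is a retrospective sample in which the same data are collected as in the prospective cohort, apart from the non-routine tests and the questionnaires. The sampling rule is "For practical reasons, we intend to include the first 200 non-included candidates in this retrospective sample". Refusers are kept out: "Patients who refused to participate in the study will not be included". A second, narrower check follows: "Baseline characteristics (age and sex) will be analysed for all (non-included) candidates to investigate possible selection bias as well".

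Two other sections set the calendar. Study population states: "We intend to include 450 patients in Zuyderland MC starting from July 2016, and 150 patients in MUMC+ from September 2016". Trial status reports that the derivation cohort was recruited "from July 2016 until the beginning of February 2017 in the two participating centres", with 450 patients at Zuyderland MC and 153 at MUMC+. The Discussion names incomplete inclusion as a possible limitation and points to this additional analysis as the response.

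**The concern.** A sample taken in time order begins on the first day of recruitment and stops once 200 records are reached. The two centres started about two months apart, so the earliest missed candidates can only come from Zuyderland MC. Recruitment then ran from summer into winter. Crowding, the stated cause of non-inclusion, can vary by season and hospital, and so can case mix. Start-up conditions may also differ from routine running.

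If such a block is set against the whole two-centre cohort, inclusion status is mixed with calendar time and centre. A difference could then reflect season or hospital rather than selection, and similarity would say little about months or a centre that were not sampled. The variables that matter most for a mortality model (vital signs, comorbidity, routine laboratory values and 30-day mortality) are the ones examined only in the 200.

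**Working it through.** The figure of 200 is justified by practicality alone, so there is no calculation to reproduce. The question is how much of the recruitment period, and of each centre, a block of 200 would cover.

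**Inputs from the protocol article**
- Included: 450 at Zuyderland MC, 153 at MUMC+, 603 in total (Trial status). Zuyderland share = 450/603 = 75%.
- Starts: July and September 2016 (Study population). End: beginning of February 2017 (Trial status).

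**Assumptions, not in the article**
- Starts on 1 July and 1 September 2016, end on 3 February 2017. Zuyderland then recruits for 31.0 weeks and MUMC+ for 22.1 weeks, with a gap of 8.9 weeks.
- One pooled count of 200.
- The same share f of candidates included at both centres, constant over time. No value of f is given, so a range is shown.

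**Formulas**
- Inclusions per week: 450/31.0 = 14.5 at Zuyderland; 153/22.1 = 6.9 at MUMC+.
- Missed per week at a centre = inclusions per week × (1 − f)/f. Write z for Zuyderland and m for MUMC+.
- If 8.9 × z ≥ 200, weeks to 200 = 200/z, all from Zuyderland.
- Otherwise, weeks to 200 = 8.9 + (200 − 8.9 × z)/(z + m), and the Zuyderland share = z × weeks/200.

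Example at f = 50%: z = 14.5 and m = 6.9. By week 8.9 about 129 have been missed at Zuyderland. The remaining 71 accrue at 21.4 per week, which takes 3.3 weeks. The total is 12.2 weeks, and the Zuyderland share is 14.5 × 12.2/200 = 88%.

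| Share included (assumed) | Weeks to reach 200 | Part of the 31 weeks | Zuyderland share of the 200 |
|---|---|---|---|
| 20% | 3.4 | 11% | 100% |
| 30% | 5.9 | 19% | 100% |
| 40% | 9.1 | 29% | 99% |
| 50% | 12.2 | 39% | 88% |
| 60% | 16.9 | 54% | 82% |
| 70% | 24.6 | 79% | 77% |
| 75% | 30.9 | about 100% | 75% |

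**When does MUMC+ drop out altogether?** All 200 precede its start if Zuyderland misses at least 200/8.9 = 22.6 per week, that is f below 14.5/(14.5 + 22.6) = 39%. The article gives months, not days. Moving the start days within July and September moves this threshold between about 28% and 49%.

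**Cross-check from ED volume.** The article gives 30,000 and about 23,000 ED visits a year. An assumed eligible share of visits, less the inclusions, gives the missed candidates without assuming equal f. At 10% eligible, 200 is reached in 4.7 weeks (100% Zuyderland); at 5%, in 11.4 weeks (81%); at 4%, in 15.4 weeks (65%); at 3%, in 28.3 weeks (39%). Again the answer runs from a short early block to nearly the whole period. At the low end, most of the missed candidates would be at MUMC+.

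**The case against.** The strongest reply is that the article gives no non-inclusion rate. A reader might infer that the 200 come from the opening weeks and from one hospital, but neither is stated. At 70% to 75% inclusion the block covers most or all of the period and has nearly the cohort's own centre mix. Because the cohort is 75% Zuyderland, a mainly Zuyderland sample is not in itself unbalanced. The text also does not exclude a count of 200 per centre. All of this stands, and it makes the size of the problem unknown. It does not remove the point. The rule guarantees no spread over time, and a count per centre would cure the centre imbalance but not the time imbalance. If inclusion were as high as 75%, only about 603 × 0.25/0.75 = 201 candidates would have been missed, and a limit of 200 for practical reasons would hardly be needed.

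Second, age and sex are analysed for all non-included candidates, at both centres and in every month. This also stands. It rules out saying that the check cannot represent the recruitment period at all. It does not extend to severity, comorbidity, laboratory values or mortality.

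Third, the article does not say that the 200 will be compared with the whole cohort. Date and time of the visit are collected, so a comparison within the same months and centre remains open. That is correct, and it is the basis of the fallback below.

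A reader might also infer that 200 is too few, so that a null result would mislead. With 200 against 600 and 10% mortality in both, the half-width of the 95% CI is 1.96 × √(0.09/600 + 0.09/200) = 4.8 percentage points. That follows from the number 200, not from time order, and redrawing the same number would not change it. The section specifies no significance test and no rule for concluding that there is no difference. The document does not support that criticism.

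**Conclusion.** The point holds in a limited form. Taking missed candidates in time order, with staggered centre starts and a seven-month recruitment period, means that the full-data check may not represent later months or MUMC+ beyond age and sex. Under the stated assumptions the block covers about 11% of the period at 20% inclusion, 39% at 50%, and all of it only near 75%. The Zuyderland share falls from 100% through about 88% to the cohort's 75%. These figures rest on a single pooled count, equal and constant inclusion at both centres, and start days that the article does not give.

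This is a weakness in a supporting analysis. It leaves the primary endpoint, the prediction model, its sample size and the external validation unchanged. It deserves correction because the protocol offers this analysis as its answer to incomplete inclusion. Incomplete inclusion is not the only limitation named: the Discussion also acknowledges the restriction to internal medicine and gastroenterology patients.

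**What to change.** Draw the 200 at random from the list of all non-included candidates, leaving out refusers as the protocol already requires, stratified by centre and calendar month in proportion to the numbers missed. The planned analysis of age and sex in all non-included candidates implies that such a list can be made. State whether 200 is a total or a count per centre, and report the number missed by centre and month.

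The number of records stays at 200. The cost is that they are spread over more dates and two sites. Trial status shows that derivation recruitment has ended, and the article does not say whether the 200 have been abstracted. Re-extraction is needed only if they have.

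If they have and a redraw is not practical, report the dates and centres of the 200, compare them with included patients of the same centre and months, and limit the conclusion to that period and centre. This fallback costs precision when the block is short. On the equal-inclusion assumption, the contemporaneous included patients number 200 × f/(1 − f), which is 200 at 50% inclusion but only 50 at 20%.

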### Study analysis

#### Statistical analysis

First, patients characteristics and outcomes will be described. Continuous variables will be reported as means with standard deviations or medians with interquartile range and categorical variables as proportions. Valid percentages will be used when values are missing.

Secondly, we will quantify the ability of the risk-stratification scores, clinical impression scores and non-routine laboratory tests to discriminate between the presence and absence of the different endpoints separately using the area under the receiver operator characteristics curve (AUC-ROC). We will determine their diagnostic accuracy using sensitivity, specificity, positive and negative predictive values (PPV, NPV), likelihood ratios and Youden’s index. For the discriminatory value of risk-stratification scores and clinical impression scores, combined data from both centres will be used. For the non-routine laboratory tests, only data from patients recruited in Zuyderland MC will be used.

Third, we will identify possible predictors of adverse outcome using univariable logistic regression analyses. Odds ratios (OR) with 95% confidence intervals (95% CI) will be calculated. Continuous variables will be checked for nonlinearity and collinearity. In case of missing items, we will use stochastic regression imputation to impute these items using predictive mean matching.

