#### Model development

We will develop a clinical prediction model for 30-day mortality using multivariable logistic regression with predictors that are deemed feasible. We consider predictors feasible when a parameter is available in at least 90% of the participants at the ED, reproducible and easily retrieved. Participants that are prospectively included in Zuyderland MC and MUMC+ will form the derivation cohort and their data will be used for model development. For external validation, we will retrospectively collect data of ED patients to form a validation cohort. For the development and validation of our model the Stiell criteria will be applied [46].

After external validation, we will test the predictive ability of the model for the secondary composite endpoint and test whether addition of clinical impression scores and/or non-routine laboratory tests results in a better prediction of adverse outcomes.

All data will be analysed using IBM SPSS Statistics for Windows, Version 24.0 (IBM Corp., Armonk, N.Y., USA) and R version 3.3.3.

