#### Sample size calculation

Since we will be using logistic regression analysis to identify predictors of 30-day mortality, a minimum of 10 events per candidate predictor is suggested [47]. Expected 30-day mortality in older medical ED patients is assumed to be at least 10% based on previous studies in the Netherlands [4, 48]. Therefore, we decided to include 450 patients in Zuyderland MC and 150 patients in MUMC+ to form the derivation cohort. For external validation of our prediction model, we need approximately 100 events, and therefore, the sample size of the validation cohort will be based on the mortality rate of the derivation cohort (estimation: 800 patients).

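### The missing-data method as named is a single imputation, so the promised 95% confidence intervals for odds ratios are too narrow: slightly at 10% missing, materially if more is missing

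*Protocol article*

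**What the plan says.** Three statements in the Protocol article bear on this.

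- **Statistical analysis, third step.** The plan says that "we will identify possible predictors of adverse outcome using univariable logistic regression analyses", and that "Odds ratios (OR) with 95% confidence intervals (95% CI) will be calculated". The same paragraph closes with the rule for missing items: "we will use stochastic regression imputation to impute these items using predictive mean matching".
- **Model development.** A predictor may enter the multivariable model only if it is "available in at least 90% of the participants at the ED, reproducible and easily retrieved". This caps missingness at 10% for model predictors. No such cap is stated for the univariable odds ratios.
- **Sample size calculation.** The derivation cohort is 450 + 150 = 600 patients, with an expected 30-day mortality of at least 10%.

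Nowhere does the article mention multiple imputation, a number of imputed data sets, a pooling rule or a variance correction. R is among the listed software.

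**The concern.** Stochastic regression imputation is the usual name for filling each gap once, with a regression prediction plus random variation. The completed data set is then analysed as if every value had been measured. The standard error reflects 600 apparent observations however many were imputed, while the true variability of the estimate grows with the missing fraction. The interval therefore covers the true odds ratio less often than 95% of the time.

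Identifying early predictors of adverse outcome is the first of the study's two aims, and these intervals are how the precision of those predictors will be reported. The understatement is greatest for the least complete predictors, so intervals would not be comparable across predictors with different completeness.

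**Working it through.** The plan gives no figure of its own to reproduce here. The check asks how far a nominal 95% interval falls short after one imputation, and whether pooling repairs it.

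**Inputs from the Protocol article:** n = 600; 10% events; univariable logistic regression; predictive mean matching.

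**Assumptions, not in the documents:** log odds ratio 0.5 per SD; values missing completely at random; outcome in the imputation model; one auxiliary variable correlated 0.3 with the predictor; 5 donors; 600 replicates per setting.

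**Compared:** (a) one imputation with estimate ± 1.96 × SE; (b) 20 imputations pooled by Rubin's rules, with T = W + (1 + 1/20)B. Here W is the average within-imputation variance and B the between-imputation variance.

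| Missing | Single: mean SE | Single: true SD | Single: coverage | Pooled: mean SE | Pooled: coverage | Single interval narrower by |
|---|---|---|---|---|---|---|
| 5% | 0.143 | 0.153 | 93.5% | 0.147 | 95.8% | 2% |
| 10% | 0.143 | 0.157 | 92.7% | 0.150 | 95.7% | 5% |
| 20% | 0.143 | 0.182 | 88.2% | 0.159 | 94.8% | 10% |
| 30% | 0.143 | 0.196 | 85.0% | 0.170 | 93.7% | 15% |
| 40% | 0.144 | 0.225 | 81.2% | 0.183 | 94.7% | 21% |

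The single-imputation SE stays at about 0.143 throughout while the true SD rises from 0.153 to 0.225. Mean estimates run from 0.49 to 0.51 against a true 0.50, so the fault lies in the interval and not in the point estimate. With n = 450 (Zuyderland only) and 20% missing, coverage was 91.3% and the interval 10% narrower.

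**Simulation error.** With 600 replicates, the standard error of a coverage of 92.7% is √(0.927 × 0.073 / 600) = 0.011. The 5% row is therefore not clearly different from 95%. The 20% and higher rows at n = 600 are.

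**Cross-check by formula.** With one imputation the variance of the estimate is about W + 2B (Rubin's total with one data set). The fraction of T due to imputation was 0.092 at 10% missing and 0.276 at 30%.

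- 10% missing: T = 0.150² = 0.0225; B = 0.092 × 0.0225 / 1.05 = 0.00197; W = 0.908 × 0.0225 = 0.02043. True SD = √(0.02043 + 0.00394) = 0.156. Coverage = 2Φ(1.96 × 0.143 / 0.156) − 1 ≈ 92.7%.
- 30% missing: T = 0.170² = 0.0289; B = 0.276 × 0.0289 / 1.05 = 0.00760; W = 0.724 × 0.0289 = 0.02092. True SD = √(0.02092 + 0.01520) = 0.190. Coverage = 2Φ(1.96 × 0.143 / 0.190) − 1 ≈ 86.0%.

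Both agree with the simulation.

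**Sensitivity to the imputation model.** With an auxiliary variable correlated 0.7 instead of 0.3 (1,500 runs), single-imputation coverage was 94.1%, 92.3% and 90.6% at 10, 20 and 30% missing. With 0.3 the same runs gave 92.9%, 88.9% and 86.4%.

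**If the outcome is left out of the imputation model.** The article does not say whether it is included. In a 2,000-replicate run without it, the log odds ratio shrank from 0.50 to 0.45, 0.41 and 0.36 at 10, 20 and 30% missing, and coverage was 93.6%, 90.3% and 82.3%. The shortfall then comes from bias toward no effect.

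**The case against.** **The text does not say that imputation is done once.** Predictive mean matching is also used inside multiple imputation, and an article may leave the number of data sets to an analysis plan. This has some force. But the article names a method, and the name it uses is that of a single imputation. If multiple imputation was meant, the sentence still needs correcting.

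**The effect on the prediction model is small.** This stands. The 90% availability rule holds model predictors to at most 10% missing, where single imputation is a defensible shortcut for model building.

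**The larger figures rest on assumptions.** This also stands. The documents give no missing rates. The article lists many vital signs, comorbidities and routine tests that could strengthen the imputation model. Missing items might also mean components of scores or questionnaires, in which case imputing whole predictors overstates the loss. A strong imputation model reduces the under-coverage but does not remove it.

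Three stronger readings are tempting, and the documents do not support them:

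- *Too many predictors will be selected.* A reader might infer this from intervals that are too narrow. But the article states no p-value threshold or significance-based selection rule; the stated criterion for the model is feasibility.
- *Missingness is heavy because tests were ordered on indication.* The article does not say so. It lists routine tests among the parameters to be collected, and the extra samples are taken by protocol.
- *The sentence joins two incompatible methods.* Predictive mean matching with a randomly chosen donor is itself a stochastic, regression-based imputation. The wording is loose, not contradictory.

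**Conclusion.** The concern holds in a limited form. The method as named does not support the 95% intervals promised in the same paragraph.

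- **At 10% missing, the cap for model predictors:** coverage of about 93 to 94% and intervals about 5% too narrow. This is a minor defect.
- **At an assumed 20 to 30% missing, possible for the uncapped univariable odds ratios:** coverage of about 85 to 92%, depending on how well other variables predict the missing values. This would be material.

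Both ranges assume values missing completely at random and the outcome included in the imputation model; point estimates are then essentially unbiased. The direction of the error does not depend on the missing rate, but its size does, and the documents give no rate. The finding concerns interval width only. It does not show that the model's coefficients are wrong.

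**What to change.** Replace the imputation sentence with multiple imputation by predictive mean matching in R. State the number of data sets (for example 20), include 30-day mortality in the imputation model, and pool the log odds ratios and the model coefficients by Rubin's rules. In the simulation above this restored coverage to about 94 to 96% at every missing fraction tried. Reporting the missing fraction for each predictor beside its odds ratio would let readers judge how much rests on imputation.

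If single imputation is kept, the minimum is to justify it by a stated low missing fraction and add a multiple-imputation sensitivity analysis.

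The cost is one sentence and a little more analysis work in software already listed. Collected data do not change, so completed enrolment of the derivation cohort is no obstacle. Intervals become wider: by about 5% at 10% missing (0.150 / 0.143 = 1.05) and about 19% at 30% (0.170 / 0.143 = 1.19).
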